### Plans to promote participant retention and complete follow-up {18b}

Strategies to minimise loss to follow-up will include using text message, email and phone reminders made to participants. Each questionnaire has a completion window to allow participants to complete the questionnaires even if they are unavailable at the 4- and 12-week time points. Participants may also be contacted by telephone by a member of the trial team in order to collect follow-up data if no responses are received.

A website has been created for the trial where updates on trial activity and relevant information relating to the trial and BV will be published. Additionally, accounts will be maintained across social media platforms to keep participants and potential participants informed of trial activity.

### Data management {19}

All trial baseline data will be collected by site staff and entered onto the trial bespoke Randomisation system and MACRO database. Both systems will be developed and maintained by the NCTU. Access to the database will be restricted and secure. Sites will be provided with paper workbooks to assist them with data collection. Missing or spurious data will be queried in a timely manner throughout the trial. Follow-up data will be collected via two participant-completed questionnaires, at 4 and 12 weeks post-treatment start date, and these will be sent either electronically via a secure link or as a paper questionnaire sent to the participant’s address, with a pre-paid return envelope. Identifiable information about participants (such as address data for questionnaires and samples) will be held in a separate database to the trial data with access restricted to those involved in follow-up only, as authorised by the CI. All access and data transactions within the databases will be logged with a full audit trail.

### Confidentiality {27}

Individual participant medical information obtained as a result of this trial is considered confidential and disclosure to third parties is prohibited with the exceptions noted in this protocol.

Participants’ contact details, including name, address, telephone/mobile number and email, will be shared between participating sites and NCTU for the purposes of issuing sample kits, questionnaires and electronic reminders (text/email) for the trial.

Minimal linked anonymised data (participation identification code, initials and date of birth), used for labelling of laboratory samples, will also be shared with Leeds Teaching Hospitals NHS Trust.

Any personal data will be held in a secure database using encryption, with restricted password-protected access. Only appropriate members of the participating site team and NCTU research team will have access to these data.

Participant confidentiality will be further ensured by utilising identification code numbers to correspond to treatment data in computer files.

### Plans for collection, laboratory evaluation and storage of biological specimens for genetic or molecular analysis in this trial/future use {33}

A sub-group of patients screened remotely (pathways 2 and 3) will be invited to participate in the sub-study which involves consenting to and providing an additional self-taken vaginal microbiota swab at baseline and 4 weeks post-treatment start date. The consent for this will be optional, and participants who do not give their consent will not be precluded from participating in the trial. On receipt, these samples will be frozen at − 70 °C and stored at Leeds Teaching Hospital NHS Trust. These samples will be used for future analysis of the vaginal microbiota to assess any changes between baseline and week 4. The analysis of these will be the subject of a future grant application and further ethical approval and only the research team will have access to the samples whilst in storage.

## Statistical methods

### Statistical methods for primary and secondary outcomes {20a}

The analysis and reporting of the trial will be in accordance with CONSORT guidelines. A full statistical analysis plan (SAP) will be developed by the blinded trial statistician and agreed prior to database lock and release of treatment allocations.

The primary approach to the primary comparative analysis will be to analyse as randomised without imputation of missing data unless the proportion of missing data is greater than anticipated (i.e. greater than 20%) with due emphasis being placed on the confidence intervals for the between-arm comparisons. It is expected that adherence with trial treatment will be high. However, if it is lower than expected, a complier average causal effect (CACE) analysis will be performed to check the stability of the conclusions. Compliers will be those reporting the use of at least 75% of the treatment. The SAP will provide details of circumstances where a CACE analysis should be performed.

Continuous variables will be summarised, dependent on distribution, in terms of the mean, standard deviation, median, lower and upper quartiles, minimum, maximum and number of observations. Categorical variables will be summarised in terms of frequency counts and percentages. Descriptive statistics of demographic and clinical measures will be used to assess balance between the randomised arms at baseline, but no formal statistical comparisons will be made.

The evaluation of the primary outcome will be performed using a mixed effects model for the binary outcome that includes factors used in the minimisation (first/isolated episode or recurrent BV, female sexual partner in the previous year, method of contraception, pathway; the inclusion of site will be dependent on model convergence). If this model does not converge, a generalised estimation model with site as a panel variable may be used instead. The primary effectiveness parameter comparing dequalinium chloride with the usual care arm will be the risk difference in the proportion of participants who report resolution of symptoms 4 weeks after treatment for BV with no additional treatment, along with the 2-sided 95% confidence interval. Dequalinium chloride will be regarded as non-inferior to usual care antibiotics if the lower bound of this 2-sided 95% confidence interval for the risk difference (dequalinium chloride minus usual care antibiotics) is − 10% or greater (e.g. a lower bound of 9% would infer non-inferiority), i.e. dequalinium chloride is not likely to be worse than usual care antibiotics by more than 10%. Secondary outcomes with the exception of side effect data will be analysed using appropriate regression models including minimisation variables and baseline values of that outcome if measured. The analyses of secondary outcomes will be considered supportive to the primary and estimates and *p*-values (where presented) should be interpreted in this light.

Side effect data will be summarised using descriptive statistics according to the treatment the participant actually received, irrespective of randomisation.

The economic analysis will compare the costs associated with dequalinium chloride with usual care antibiotics. The economic evaluation will use only data collected within the trial and so estimates of costs and outcomes will therefore relate only to the initial period and assessment at week 4 and week 12. The primary analysis will be based on cost per patient with resolved symptoms at week 4 (as per the trial primary outcome), with a secondary analysis of cost per patient without recurrence of symptoms at week 12.

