## Trial design {8}

This is a phase IV, multi-centre, randomised, open-label, parallel group, non-inferiority trial with equal allocation (1:1) to receive either dequalinium chloride (intervention) or usual care antibiotics (control). Women will be recruited either face-to-face or remotely from a minimum of 15 sexual health clinics in the UK or following initial self-referral and completion of an expression of interest (EOI) form via the DEVA trial website (www.devastudy.ac.uk). The participant information sheet and animations to support the trial documentation can be found on the trial website. An embedded Study Within a Trial (SWAT) investigating the timing of reminder communications has been built into the trial design. Details of the SWAT can be found on the SWAT repository 118 [19] and will be reported separately.

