### Sample size {14}

Assuming 78% of participants have BV symptom resolution at 4 weeks post-treatment start date in both the control and intervention groups [9, 16, 17], a total sample size of 722 for analysis (361 in each group) will achieve 90% power to conclude non-inferiority with a lower confidence limit for the absolute risk difference of 10%, using a 1-sided significance level of 0.025. To allow for a loss of primary outcome data of up to 20%, the trial will recruit a total of 904 women. The 10% non-inferiority margin was acceptable to 68% of a sample of women attending two GUM clinics and 81% of clinicians experienced in treating BV.

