### Interim analyses {21b}

There will be no planned interim effectiveness analyses. However, an internal pilot phase has been built into the trial to allow a feasibility assessment which will examine recruitment, retention and adherence. Stop–go criteria 9 months after the first participant has been randomised will be used to determine the progression of the trial. Recruitment will be measured against the overall recruitment target. Retention will be determined by provision of primary outcome data. Adherence level will be measured using simple categories asking how much of the trial medication the participant used/took (high > 75% used/taken, more than half (50–75% used/taken), less than half (1–49% used/taken), from both treatment arms.

The SWAT will also undergo its own interim analysis which will be detailed in the SAP for the SWAT.

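### The only adherence-based analysis of the primary outcome is conditional on poor adherence, so non-inferiority can be declared with no check on dilution

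*Protocol article*

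**What the plan says.** The protocol article's section on statistical methods for primary and secondary outcomes {20a} makes the primary comparison as randomised. It expects adherence to be high but gives no figure. It then says: "However, if it is lower than expected, a complier average causal effect (CACE) analysis will be performed to check the stability of the conclusions". Compliers are defined by self-report: "Compliers will be those reporting the use of at least 75% of the treatment". The SAP, which is not shown, is to set out the circumstances in which the CACE is run.

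The same section states the decision rule. Dequalinium is non-inferior if the lower bound of the two-sided 95% interval for the as-randomised risk difference is −10% or greater. No adherence-based result enters that rule.

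No other adherence-based analysis of the primary outcome appears. The section on non-adherence and missing data {20c} describes only missing-data methods, and treatment actually received is used only for side effects.

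**The concern.** A conditional adherence check suits a superiority trial, where dilution usually works against the claim. In a non-inferiority trial it can work for the claim. If similar fractions of both arms do not take their treatment and then fare alike, the two arms look more similar than the treatments are.

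As written, adherence good enough not to trigger the CACE leaves the claim resting on the one analysis exposed to this effect. Modest non-adherence, of a size many would still call high adherence, is enough to matter. Follow-up is remote, with no visits after randomisation {11c}, and the Discussion says the authors are unsure whether the recruitment approach will affect adherence. That sits uneasily with making the check depend on an expectation of high adherence. At stake is how far a guideline group could rely on a positive result as evidence about the treatment when taken.

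**Working it through.** **Inputs from the protocol article, Sample size {14}.** Resolution is taken as 78% in each arm. The size is stated as: "a total sample size of 722 for analysis (361 in each group) will achieve 90% power to conclude non-inferiority". The margin is 10 percentage points, tested one-sided at 0.025. Recruitment is set at 904 to cover 20% missing primary outcomes.

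**Reproducing the plan's figure.** With unpooled variance, n per arm = 2 × 0.78 × 0.22 × (1.960 + 1.282)² / 0.10² ≈ 360.6, so 361 per arm and 722 in total, with power 90.0%. Allowing for 20% loss, 722 / 0.80 = 902.5, so 903, or 904 as an even total. The plan's figures hold.

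**Assumptions, not in the document.** True resolution among adherers is 78% on control and 68% on dequalinium, so the difference among adherers lies exactly at the margin. Adherence a is the same in both arms. Non-adherers in both arms share one resolution rate r, taken from 0.30 to 0.78.

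**Formulae.**
- pC = 0.78a + r(1 − a)
- pT = 0.68a + r(1 − a)
- so pT − pC = −0.10a
- SE = √[pC(1 − pC)/361 + pT(1 − pT)/361]
- Probability of declaring non-inferiority = Φ((pT − pC + 0.10)/SE − 1.96)

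**Example, a = 0.90 and r = 0.78.** pC = 0.78; pT = 0.612 + 0.078 = 0.69; difference −0.09; SE = √[(0.1716 + 0.2139)/361] = 0.0327. Then 0.01/0.0327 − 1.96 ≈ −1.654, and Φ = 4.9%.

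| Adherence in both arms | As-randomised difference (points) | r = 0.30 | r = 0.50 | r = 0.78 |
|---|---|---|---|---|
| 100% | −10.0 | 2.5% | 2.5% | 2.5% |
| 95% | −9.5 | 3.5% | 3.5% | 3.5% |
| 90% | −9.0 | 4.8% | 4.8% | 4.9% |
| 85% | −8.5 | 6.3% | 6.4% | 6.7% |
| 80% | −8.0 | 8.1% | 8.4% | 8.9% |

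The error reaches 5% at about 89 to 90% adherence, and r has little influence.

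**Unequal adherence.** The direction then depends on which arm adheres less:
- Non-adherence in the dequalinium arm only, 10%, r = 0.30: pT = 0.9 × 0.68 + 0.1 × 0.30 = 0.642. The difference is −13.8 points and the error about 0.1%.
- Control 90%, dequalinium 80%, r = 0.30: pC = 0.732, pT = 0.604. The difference is −12.8 points and the error 0.3%.
- Control 80%, dequalinium 90%, r = 0.30: pC = 0.684, pT = 0.642. The difference is −4.2 points and the error about 38%.

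**Precision of the CACE.** With common adherence, the CACE is approximately the as-randomised difference divided by a, and its SE is divided by a as well. Testing it against −10 points is therefore like testing the as-randomised difference against −10a points. If the arms are truly equal at 78%, SE = √(0.3432/361) = 0.0308 and power ≈ Φ(0.10a/0.0308 − 1.96). That gives 87% at 95% adherence, 83% at 90% and 74% at 80%, against the 90% planned.

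**The case against.** **Deferral to the SAP.** The SAP is to say when the CACE is run and must be agreed by the blinded statistician before database lock and release of allocations. Its trigger may be strict enough to catch modest non-adherence. This stands against any complaint that no threshold is given, and the trigger need not be an ad hoc judgement. It does not remove the conditionality, which the protocol itself fixes.

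**The estimand.** The primary parameter is the as-randomised risk difference in a trial described as pragmatic. For that quantity the error rate stays at 2.5%. The inflation arises only when the effect among adherers is the target. This stands, so the primary analysis is not invalid.

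**Direction.** A reader might infer that non-adherence in either arm always shrinks the difference and favours the claim. That is wrong: non-adherence in the dequalinium arm alone widens the deficit whenever those women resolve at a rate below 68%. The outcome also counts a need for additional treatment as failure, which limits dilution through rescue treatment.

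**The categories.** A reader might also see a fault in setting a complier cut-off of at least 75% beside the pilot categories in Interim analyses {21b}: "high > 75% used/taken, more than half (50–75% used/taken". The two differ only at exactly 75%. The dequalinium course is six tablets, where four is 67% and five is 83%, so the mismatch has no practical effect on that count. Nor can a missing option for women who took nothing be inferred from a condensed description of the pilot measure when the questionnaire is not shown.

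**Conclusion.** The point holds as a cheap improvement that should be made. The protocol permits a non-inferiority claim with no adherence-based analysis, because the only one planned is conditional and lies outside the decision rule.

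Under equal non-adherence, the chance of a false claim about adherers is roughly doubled at 90% adherence and is more than three times nominal at 80%. These figures rest on assumed adherence levels, equal outcomes in non-adherers and a true difference among adherers exactly at the margin. The protocol gives no adherence figure. With unequal adherence the bias can go either way and can be larger, which is itself a reason to run the analysis routinely.

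The documents do not support the stronger reading that the trial's type I error is uncontrolled or that its primary analysis is wrong. What is weakened is the robustness of the conclusion about the treatments as taken.

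**What to change.** In section {20a}, remove the condition on adherence and pre-specify the CACE as a supportive analysis that is always performed. Report it beside the as-randomised result, against the same margin of −10 percentage points. Have the SAP state how discordant results will be interpreted. Keep the as-randomised analysis primary.

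An unconditional analysis also avoids any question about when the trigger was set. The Trial Management Group reviews adherence monthly {11c}, whereas the SAP need only be agreed before database lock.

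The cost is a wording change and one more analysis of adherence data already collected. The real downside is precision. With approximate power of 83% at 90% adherence and 74% at 80% when the arms are truly equal, the CACE may fail to support a correct claim. For that reason it should inform interpretation and not become a second hurdle in the decision rule without a fresh look at sample size. A per-protocol comparison is no simple substitute: it selects on behaviour after randomisation in an open-label trial with a participant-reported outcome.

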### Methods in analysis to handle protocol non-adherence and any statistical methods to handle missing data {20c}

Several strategies to investigate the effect of missing primary outcome data will be undertaken as sensitivity analyses, including the use of multiple imputation with chained equations and minimisation variables as covariates. Where the proportion of missing primary outcome data is greater than 20%, the primary analysis will use multiple imputation. More information on methods will be included within the SAP.

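### Sub-study consent is a minimisation factor but is missing, without a stated reason, from the covariates listed for the primary model; the interval may be slightly too wide

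*Protocol article*

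**What the plan says.** Sequence generation {16a} lists six minimisation factors: episode type, a female sexual partner in the previous year, contraception, consent to self-taken sub-study samples, site and recruitment pathway.

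Statistical methods for primary and secondary outcomes {20a} says that the primary mixed effects model "includes factors used in the minimisation (first/isolated episode or recurrent BV, female sexual partner in the previous year, method of contraception, pathway", and for site that "the inclusion of site will be dependent on model convergence". Five of the six factors are thus accounted for. Convergence is the only ground offered for leaving a factor out, and it is applied to site alone.

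Two other statements carry no exception. Secondary outcomes are to be analysed with "appropriate regression models including minimisation variables and baseline values of that outcome if measured" (same section). The missing-data strategies are described as "including the use of multiple imputation with chained equations and minimisation variables as covariates" (section {20c}).

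The biological specimens section {33} limits who can have the factor present: "A sub-group of patients screened remotely (pathways 2 and 3) will be invited to participate in the sub-study".

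**The concern.** The covariate list is not simply left to the analysis plan. The protocol fixes it by naming the factors, and the list departs from the allocation scheme and from the protocol's own secondary and imputation models. Read literally, sub-study consent is in every adjusted analysis except the one that decides the trial.

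When allocation is balanced on a prognostic factor and the analysis ignores it, the model-based standard error does not credit the balance achieved. The interval is then wider than it needs to be. In a non-inferiority trial judged on a lower confidence limit, this costs a little power. Settling the list before allocations are released also removes a discretionary covariate choice from the primary analysis.

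**Working it through.** **The plan's own figure.** Sample size {14} gives: "Assuming 78% of participants have BV symptom resolution at 4 weeks post-treatment start date in both the control and intervention groups", a 10-point margin, "using a 1-sided significance level of 0.025", 90% power, 361 per arm.

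- n per arm = 2 × 0.78 × 0.22 × (1.960 + 1.282)² / 0.10² = 360.6, so 361, or 722 in total.
- Allowing for 20% loss: 361 / 0.8 = 451.25, so 452 per arm, or 904.
- SE = √(2 × 0.78 × 0.22 / 361) = 0.0308. Power = Φ(0.10/0.0308 − 1.960) = 90.0%.

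The stated size reproduces, and it does not depend on covariate adjustment.

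**Effect of leaving out one balanced binary factor.** Let q be the proportion consenting and g the difference in resolution between women who do and do not consent. The documents give neither, so both are assumed: q from 0.2 to 0.5 and g from 0 to 20 points. The calculation is on the risk-difference scale and takes balance on the factor as exact.

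- True variance / reported variance: r = 1 − q(1 − q)g² / (0.78 × 0.22)
- SE overstated by 1/√r − 1
- Actual one-sided alpha = 1 − Φ(1.960/√r)
- Power with the factor omitted = Φ((0.10 − 1.960 × SE) / (SE√r))
- Power with the factor included = Φ(0.10/(SE√r) − 1.960)

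The largest case, q = 0.5 and g = 0.20: r = 1 − 0.25 × 0.04/0.1716 = 0.9417, and 1/√r = 1.0305.

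| q | g | r | SE overstated | alpha | power, omitted | power, included |
|---|---|---|---|---|---|---|
| any | 0 | 1.0000 | 0% | 0.0250 | 90.0% | 90.0% |
| 0.2 | 0.05 | 0.9977 | 0.12% | 0.0249 | 90.06% | 90.10% |
| 0.2 | 0.10 | 0.9907 | 0.47% | 0.0245 | 90.14% | 90.29% |
| 0.2 | 0.20 | 0.9627 | 1.92% | 0.0229 | 90.45% | 91.08% |
| 0.5 | 0.05 | 0.9964 | 0.18% | 0.0248 | 90.07% | 90.13% |
| 0.5 | 0.10 | 0.9854 | 0.74% | 0.0242 | 90.19% | 90.44% |
| 0.5 | 0.20 | 0.9417 | 3.05% | 0.0217 | 90.70% | 91.65% |

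The largest shortfall is 91.65 − 90.70 = 0.95 point. It is measured against the adjusted analysis; the planned 90% is kept in every row.

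**Why these are upper-end figures.** Consent can be given only in pathways 2 and 3, and pathway is in the model. If a share s of women is remote and a proportion c of them consent, then q = sc. Once pathway is in the model, the remaining contribution is s·c(1 − c)g² rather than sc(1 − sc)g², which is smaller whenever s is below 1. For example, if exactly half the women are remote and q = 0.5, then every remote woman consents, c(1 − c) = 0, and omission has no effect.

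**The case against.** The case for leaving the list alone has four parts.

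- The protocol does not promise to adjust for every factor; it says which it will include. A factor balanced for the sake of stored samples, whose analysis awaits a future grant, might reasonably be left out. That is possible, but the motive is a guess, and nothing in the text separates this factor from the others.
- The article is condensed and the unseen analysis plan may settle the matter. This limits the point to a consistency correction. It does not remove it, because the list is stated rather than deferred.
- Coding pathway 1 as not consenting would merge women who were never invited with remote women who declined. With pathway also in the model, pathway 1 has its own level and the consent term is estimated only among remote women, so the objection affects labelling more than estimation.
- The model may already struggle to converge. One further fixed term is a small addition, but this is a fair reason to settle the coding in advance.

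A reader might also infer something stronger: that consent to extra samples marks women likely to return questionnaires, so that omitting it biases a complete-case primary analysis. The documents do not support this. No section says that consent predicts response. The Discussion names in-clinic versus remote recruitment as what might affect retention, and that is pathway, already in the model. If consent affected response equally in both arms, the bias in the risk difference would be zero. Bias needs a consent–response relation that differs by arm. Suppose q = 0.5 and response among consenters and non-consenters is 0.95 and 0.65 in one arm, 0.85 and 0.75 in the other. Consenters are then 0.95/1.60 = 0.594 and 0.85/1.60 = 0.531 of responders, a difference of 0.0625. Multiplied by g = 0.05, 0.10 and 0.20, this gives a bias of 0.3, 0.6 and 1.25 points against the 10-point margin. All of these inputs are assumed. One added covariate would in any case not free the analysis from bias.

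**Conclusion.** The point holds as a minor inconsistency with a small, conservative consequence. The primary model omits one of six minimisation factors without a reason, and differs in this from the secondary and imputation models. If consent is prognostic within pathways 2 and 3, the primary interval is slightly too wide: by 0 to about 3% in standard error, with at most about 1 point of power forgone, for assumed consent of 20–50% and a resolution gap of 0–20 points. If consent is not prognostic there, nothing is lost.

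One-sided alpha stays at or below 0.025 throughout, so a false claim of non-inferiority becomes no more likely. It would be wrong to read the omission as invalidating the interval or the sample size. An imputation model richer than the analysis model is not an error in itself either; the case for alignment is consistency and a little precision.

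**What to change.** Add sub-study consent to the covariates named for the primary model in section {20a}, and fix its coding in the analysis plan before allocations are released. Because pathway 1 women are not invited, a combined pathway and consent category states the structure most clearly. The primary model would then match both the allocation scheme and the imputation model.

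The secondary and imputation models need no change, since both already use the minimisation variables without exception. If the omission is deliberate, a sentence giving the reason would resolve the inconsistency, though not recover the precision.

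The cost is one phrase and one extra parameter if the consent effect is taken as common to pathways 2 and 3 (two if it is allowed to differ between them). The factor is used in the minimisation, so it is recorded before randomisation. No new data are needed, and the sample size does not change.
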